**Additional outcomes**						
Expectation of treatment outcome	5 point ordinal scale		X			
Treatment credibility	Modified Treatment Credibility/Expectancy Questionnaire		X			
Intention to exercise	7 point ordinal scales (commitment, motivation, determination to exercise)		X	X	X	X
COVID-19 impact on physical activity	7-point ordinal scale	X		X	X	X
Adherence	Self-rated adherence to walking and strengthening program, 11-point NRS and number of days in past week exercise performed			X	X	X
	Number of in-person sessions attended			X	X	X
	Number of telehealth sessions attended			X		
	Review of patient diary					X
Harms	Adverse events			X	X	X
Blinding	Participant blinding assessed via allocation guesses (and reasons); then forced choice					X
	Outcome assessor blinding (same method)			X		
	Therapist blinding (same method)					X^b^
Therapist related factors	Beliefs about exercise; self-rated via Therapist Beliefs about Exercise Questionnaire	X				X^c^
	Beliefs about pain; self-rated via Pain Attitudes and Beliefs Scale for Physiotherapists	X				X^c^
	Pain knowledge; assessed via rNPQ	X				X^c^
	Perceived intervention credibility; assessed via modified intervention credibility and expectancy questionnaire	X		X^d^		X^d^
	Perceived connection with participant; self-rated via 101-point NRS Connectedness Scale			X		

^a^Data on MBS, PBS and emergency department presentations and hospital admissions will be sourced from government-held administrative datasets for the entire 12 month follow-up period at its conclusion. ^b^Measured at end of trial (recruitment complete); aim is to determine if the ‘Best practice control group’ therapists thought they were the intervention group of interest. ^c^Measured at baseline (pre-training), post-training, and end of trial (recruitment complete). ^d^Measured after pre-trial training (baseline), after the first 12 weeks of treatment (pilot participant), mid-way through the trial (i.e., half-way through recruitment), and at the end of the trial (recruitment complete)

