#### COVID-19 impact on physical activity

Self-reported impact of COVID-19 on physical activity is assessed via the question, “During the past 4 weeks, has COVID-19 influenced your usual physical activity levels/exercise routines?” with dichotomous response options of “Yes” or “No”. If participants answer yes, they self-report the extent to which COVID-19 has influenced usual physical activity levels/exercise routines on a 6-point Likert scale ranging from “Large reduction” to “Large increase”. Additionally, trial coordinators in Adelaide and Melbourne keep weekly records of the state recommendations and/or restrictions in relation to travel, physical activity, use of public transport, ability to leave the home, etc.

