#### Primary analysis

Data will be analysed using intention-to-treat principles with the trial biostatistician blinded to group allocation. We will use linear mixed effects models with random intercepts for individuals (to account for correlation for repeated measures) and will analyse the effect of treatment separately for each outcome. The model will include terms for stratification factors of sex and site. A time-varying, group specific effect (for each group) will be included as covariates for participants with restricted physical activity as a result of location-specific COVID-19 restrictions (based upon official activity restrictions and/or participant reported restrictions; assessment detailed above). Statistical significance will determine whether group-specific covariates or even any COVID-19 related effects are warranted for model parsimony. Multiple imputation will be used for missing data if the assumptions are reasonable [102]. We will construct linear contrasts to compare the adjusted mean change in outcome from baseline to each time point between the EPIPHA-KNEE group and the control group (and 95% confidence interval) to obtain estimates of the intervention effect. We will analyse primary and secondary outcomes without adjustment for multiple measures, but we will present unadjusted *p*-values and confidence intervals for all pre-specified analyses [103, 104] so readers can make adjustments (e.g., Bonferroni) at the level of Type I error control that they wish, at risk of making Type II errors.

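### The primary model may adjust for participant-reported COVID-19 restriction, a post-randomisation self-rating of activity change that can bias the step-count contrast in either direction

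*Protocol article*

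**What the plan says.** The Primary analysis section of the protocol article specifies linear mixed models under intention-to-treat principles, with terms for sex and site. It then adds: "A time-varying, group specific effect (for each group) will be included as covariates for participants with restricted physical activity". The source of that covariate is given as "based upon official activity restrictions and/or participant reported restrictions; assessment detailed above". The next sentence sets the retention rule: "Statistical significance will determine whether group-specific covariates or even any COVID-19 related effects are warranted for model parsimony".

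The assessment referred to is in the section on COVID-19 impact on physical activity. Participants answer: "During the past 4 weeks, has COVID-19 influenced your usual physical activity levels/exercise routines". If yes, "they self-report the extent to which COVID-19 has influenced usual physical activity levels/exercise routines on a 6-point Likert scale", running from a large reduction to a large increase. Table 5 schedules the item (row "COVID-19 impact on physical activity") at baseline, 12 weeks, 6 months and 12 months, so three of its four measurements follow randomisation.

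A source that allocation cannot affect is also kept: "trial coordinators in Adelaide and Melbourne keep weekly records of the state recommendations and/or restrictions". The COVID-19 considerations section adds that restrictions in both cities, with their dates, will be documented throughout the trial.

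**The concern.** A covariate measured after randomisation is safe to adjust for only if treatment cannot affect it. An official restriction in force at a site on a given date meets that condition. The self-report does not clearly meet it. It does not ask whether a restriction applied. It asks whether the participant's own activity changed because of COVID-19, and activity is what the first primary outcome measures.

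There are at least two routes by which the answer could depend on arm:

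- **Through realised activity.** Someone who has been less active may be readier to say that COVID-19 reduced their activity. If treatment raises activity, fewer treated participants report restriction, and adjustment takes out part of the effect.
- **Through reporting at a given activity level.** The intervention targets beliefs about activity. EPIPHA-KNEE participants might plan more and so notice more disruption, or cope better and report less. The first raises the adjusted estimate and the second lowers it.

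At stake is whether the step-count contrast is the intention-to-treat effect that the same section promises. Two further features of the passage bear on this. Retention by significance leaves the model undetermined until the data are seen. Group-specific COVID-19 terms make the treatment contrast depend on the covariate level at which it is read.

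**Working it through.** The protocol gives no figure for the effect of this adjustment, so there is none to reproduce. Its sample-size section supplies the anchor: d = 0.5 and SD of change 950 steps/day, so the planned effect is 0.5 × 950 = 475 steps/day. The sample size of 198 plays no part in the argument.

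**Simulation 1: a report can come from anyone.** Large-sample linear regression of the 12-month outcome on arm and covariate, 2,000,000 simulated participants per scenario.

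- From the protocol: effect 475, SD 950.
- Assumed: 35% officially restricted, independent of arm; restriction lowers activity by 800 steps/day.
- Assumed reporting model: log-odds of reporting restriction = −1.5 + 2.0 × official + γ × (activity − mean)/950 + δ × arm.

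| Scenario | γ | δ | Adjusted for self-report (common effect) | Against 475 |
|---|---|---|---|---|
| A. Report follows official restriction only | 0 | 0 | 475 | 0% |
| B. Less active people report more | −0.5 | 0 | 444 | −7% |
| B | −1 | 0 | 402 | −15% |
| B | −2 | 0 | 325 | −32% |
| C. EPIPHA-KNEE reports more | 0 | +0.5 | 510 | +7% |
| C | 0 | +1 | 542 | +14% |
| D. EPIPHA-KNEE reports less | 0 | −0.5 | 445 | −6% |
| D | 0 | −1 | 418 | −12% |
| E. Activity and arm together | −0.5 | +1 | 572 | +20% |

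Adjusting for official restriction only, with a common effect, gave 474–477 in every scenario. Group-specific self-report terms do not remove the bias: scenario B with γ = −1 gave 409 for participants not reporting restriction and 391 for those reporting it; scenario E gave 561 and 586.

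**Simulation 2: a report counts only if an official restriction applied.** The plan ties the covariate to location-specific restrictions, which may limit it in this way. Assumed: half of exposed participants report at mean activity, and restriction has no effect on steps. For log-odds of 0.5, 1.0 and 1.5 per SD lower activity:

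- 30% exposed: 471, 458, 450, a loss of about 1–5%.
- 60% exposed: 465, 438, 419, a loss of about 2–12%.

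Without this limit, a separate run with the same slopes and exposure shares gave 454, 422, 386 at 30% and 457, 413, 369 at 60%, a loss of about 4–22%.

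**What a loss would mean for power.** At 90% power the expected z is 1.96 + 1.28 = 3.24. If the estimate shrinks by 15% and the standard error is unchanged, 3.24 × 0.85 − 1.96 = 0.79, or power of about 79%. This is approximate, because adjustment may also reduce the standard error.

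**Group-specific terms, even with official data.** Assume an effect of 600 when unrestricted, 243 when restricted, and 35% restricted. The average is 0.65 × 600 + 0.35 × 243 = 475 (478 simulated). The arm coefficient at the unrestricted level was 602. An official covariate alone therefore does not settle which contrast is reported.

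**The case against.** The case on the other side is substantial, and much of it stands.

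- **The wording is optional.** The and/or lets the analyst use official records alone, and COVID-19 terms may be dropped altogether. The section is called preliminary, a full analysis plan is promised before formal analysis, and the statistician is blinded. The choice of source could thus be settled without sight of results by arm. This lowers the severity. It does not remove the point, because the text expressly admits the self-report to the primary model and nothing confines it to a sensitivity analysis. Blinding does not prevent bias from a covariate that treatment affects.
- **The item is not the outcome.** A reader might infer that the model adjusts for the primary outcome itself. The documents do not support that: the item asks about a change attributed to COVID-19 over four weeks, while the outcome is device-measured steps over seven days. The other primary outcome, WOMAC Total, measures knee symptoms, so the link there is weaker.
- **Loss of effect is not certain.** A reader might also infer that the adjustment necessarily removes part of the treatment effect. That needs less active people to report more restriction, or the EPIPHA-KNEE arm to report less, and the protocol has no data on either. The opposite pattern inflates the estimate, and reporting that follows official restrictions only leaves it unbiased.
- **The sizes are assumed.** The simulations use one time point and an ordinary linear model, not the planned repeated-measures model, and the reporting slopes drive the result. Limiting reports to officially exposed participants cuts the loss by roughly half or more in most cases.

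**Conclusion.** The point holds in a conditional form. The stated plan permits a post-randomisation self-rating of activity change as a covariate in the primary model, and treatment can influence that rating. The adjusted step-count contrast therefore need not equal the intention-to-treat effect.

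Against a true 475 steps/day, the possible bias ran from none, to about 1–32% attenuation when less active people report more restriction, to about 20% inflation when EPIPHA-KNEE participants report more disruption. These figures rest on assumed exposure shares, restriction effects and reporting slopes. They show what the wording allows and do not forecast this trial. The direction cannot be known in advance.

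The significance rule and the group-specific terms add a separate problem, since they leave the primary contrast undefined even if the self-report is removed. Severity: should-fix.

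**What to change.** Settle four things in the analysis plan before unblinding:

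1. In the primary model, define the COVID-19 covariate only from the official, dated, site-specific restriction record, matched to each participant's assessment window. Delete the option of participant-reported restrictions.
2. Use the self-report item only descriptively or in a labelled sensitivity analysis.
3. State in advance whether the COVID-19 term is in the model, in place of the significance rule.
4. Use a common COVID-19 effect across arms, or state the covariate level or averaging at which the treatment contrast is taken.

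The cost is a few lines of text, because the official record is already being kept. The downside is that individual differences in compliance with restrictions are no longer modelled in the primary analysis.

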### Primary outcomes

The primary outcomes are: i) average daily step count assessed over 7 consecutive days via wrist-worn accelerometry (Actigraph GT9X Link, Pensacola, FL); and ii) overall knee symptoms measured via the Western Ontario and McMaster Universities (WOMAC) Osteoarthritis Index [62]. The primary timepoint for both outcomes is 12 months.

For daily step count, participants wear the accelerometer on their non-dominant wrist at all times (removal only for shower or during water-based activities). Data are collected from the device in 60 s epochs. A paper-based activity log is provided to participants to capture times they go to bed at night and get up from bed in the morning, as well as times the accelerometer was removed and then placed back on (particularly if taken off when sleeping). Valid wear time is operationalised as having ≥10 h of waking wear time for a minimum of 4 days (3 weekdays and 1 weekend day) [63, 64]. Average daily step count is calculated as the weighted average (5:2) of weekday and weekend step counts. We chose daily step count as a primary outcome based on its: i) health benefits in knee OA (increased physical activity via walking improves both pain and function [65], and even a moderate increase in physical activity [1000 steps/day] reduces risk of functional decline [66]); and ii) established reliability/validity in knee OA [67].

The WOMAC is a disease-specific self-report questionnaire that includes pain (5 items), stiffness (2 items), and physical function (17 items) subscales. Items are scored from 0 to 4, giving a range of possible scores from 0 (no symptoms or dysfunction) to 96 (maximal symptoms and dysfunction). It has demonstrated validity, reliability, and responsiveness [68]. The use of the total score for primary outcomes is supported by the scale creators.

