### Analysis

A full statistical analysis plan will be published prior to undertaking the formal analysis of collected data (including description of secondary analyses). The proposed preliminary analysis plan is detailed below.

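### A significance test on the trial data decides which COVID-19 terms stay in the primary model, so the 12-month target effect is not fixed in advance and nominal 95% coverage is not guaranteed

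*Protocol article*

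**What the plan says.** The Primary analysis section of the protocol article gives the model for both primary outcomes: "We will use linear mixed effects models with random intercepts for individuals", with sex and site as stratification terms and a separate analysis for each outcome. On the pandemic it says: "A time-varying, group specific effect (for each group) will be included as covariates for participants with restricted physical activity". Restriction status is "based upon official activity restrictions and/or participant reported restrictions". The next sentence is the rule at issue: "Statistical significance will determine whether group-specific covariates or even any COVID-19 related effects are warranted for model parsimony".

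The treatment effect is then obtained from linear contrasts that "compare the adjusted mean change in outcome from baseline to each time point between the EPIPHA-KNEE group and the control group", with a 95% confidence interval. Under Primary outcomes, "The primary timepoint for both outcomes is 12 months". The Analysis section introduces all of this with "The proposed preliminary analysis plan is detailed below" and promises a full statistical analysis plan before formal analysis.

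**The concern.** A COVID-19 effect that is specific to each group is a treatment-by-restriction interaction. Keeping or dropping it changes what the group contrast estimates as well as its precision. If the trial's own data decide between the two by a p-value, the question answered is known only after the data have been seen. Because each outcome is modelled separately, step count and WOMAC may end up answering different questions. The reported interval is computed as though the surviving model had been chosen beforehand.

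At stake are the meaning of the primary estimate and the coverage of its interval. Masking the statistician does not help, because the test works equally well on coded group labels.

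**Working it through.** **What each model estimates.** Let d be the effect on 12-month change with restriction status held constant, g the additional treatment effect under restriction (assumed the same at every visit), and r0 and r12 the proportions restricted at baseline and 12 months, taken as equal in the two groups.

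- Term kept, contrast at a common restriction level: g cancels from the change, and the target is d.
- Term dropped: the target is d + g × (r12 − r0), the effect averaged over the restrictions that occurred.

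The two targets differ only if g ≠ 0 and r12 ≠ r0.

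**Inputs from the Trial sample size section.** Effect size 0.5, SD of change 950 steps/day, four time points, correlation 0.7, 20% loss, 99 per group.

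- Effect: 0.5 × 950 = 475 steps/day.
- Completers: 99 × 0.8 ≈ 79 per group.
- SD at a single visit: 950 / √(2 × (1 − 0.7)) ≈ 1,226 steps/day.

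The protocol gives no figure for the selection rule itself. Its sample size does reproduce on these inputs: 2 × ((1.960 + 1.282)/0.5)² ≈ 84.06 per group; × (1 + 3 × 0.7)/4 = 0.775 gives 65.15; 65 × 1.2 = 78 per group, or 156; × (1 + 5.5 × 0.05) = 1.275 gives 198.9, stated as 198.

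**Assumed, not in the document.** Restriction 30% or 50% at follow-up, with several baseline patterns; COVID-19 main effect −400 steps/day; g of 0, −300 or −475 steps/day; testing at 0.05, interaction first and then main effect; known covariance.

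**Simulation for step count.** Four-visit mixed model, 1,500 runs per setting. The 12-month contrast of change is read at a common restriction level from whichever model survives. With 0% restricted at baseline:

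| Restricted at follow-up | g | All-participant target | Coverage of that target |
|---|---|---|---|
| 30% | −300 | 475 − 300 × 0.3 = 385 | 92% |
| 50% | −300 | 475 − 300 × 0.5 = 325 | 86% |
| 30% | −475 | 475 − 475 × 0.3 = 332.5 | 85% |
| 50% | −475 | 475 − 475 × 0.5 = 237.5 | 68% |

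The simulation standard error in the last row is √(0.68 × 0.32/1,500) ≈ 1.2 points. A repeat with 3,000 runs per setting gave 92%, 86%, 86% and 71%.

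In the second row the reported effect averages about 521 steps/day when the term is kept and about 332 when it is dropped, a gap of 189. The first figure exceeds even its own target of 475, because the term survives mainly in trials where its estimate happens to be large.

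**Same mechanism in SD units.** With d = 0.5 SD, 50% restricted at follow-up, 0% at baseline and g = −0.2 SD, the term is kept in about 40% of trials. The reported effect averages 0.55 SD when kept and 0.40 SD when dropped. Coverage is 91% for the constant-restriction effect (0.50) and 90% for the all-participant effect (0.40).

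**Where the loss disappears.**

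- g = 0: coverage about 94–95%.
- Equal restriction at baseline and 12 months (30%/30% or 50%/50%): 94–95%, even at g = −475.
- Contrast averaged over observed restriction status at each visit: about 94–96%, even with the selection step left in.
- No treatment effect and no interaction: type I error 4.9–5.4%.

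**After the fix.** A fixed model with restriction as a main effect only gives about 95% for the all-participant effect. A fixed model with group-specific terms and an averaged contrast gives 94–96%.

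**The case against.** The strongest reply is that the text is labelled preliminary and a full analysis plan is promised, so the threshold, the order of testing and the restriction level of the adjusted means can properly wait for it. That stands for those details, and their absence is no finding. It does not cover the rule itself, which the protocol states outright and which an analysis plan that follows it would inherit.

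Three stronger readings are tempting, and the document does not support them.

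- A reader might infer that the interaction test has so little power that the choice is close to random. A calculation on one change score per person does keep the term in only 15–17% of trials at g = −300. The protocol plans a repeated-measures model with a time-varying covariate, so all visits inform the term. On that model it is kept in 49–69% of trials at −300 and 87–97% at −475.
- A reader might infer that the model with the term kept gives the effect in unrestricted participants. The protocol contrasts change from baseline, so the target is the effect with restriction status held constant.
- A reader might infer that the interval is simply invalid. The loss needs a true interaction, a shift in restriction between baseline and 12 months, and a contrast not averaged over status, all at once. COVID-19 impact is also recorded at baseline, so 0% baseline restriction is only one scenario. No inflation of false positives was found with no treatment effect and no interaction.

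It is also fair to say that a main-effect-only model is not the only sound choice. Keeping the planned group-specific terms and averaging the contrast is equally valid and closer to the authors' design.

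**Conclusion.** The point holds. As written, a p-value chooses between two target effects in the primary analysis, possibly differently for step count and WOMAC, and the interval makes no allowance for that choice. Nominal coverage of the all-participant effect is therefore not guaranteed.

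The size depends wholly on assumed restriction rates and interactions, since the document gives neither. Coverage is about 92% to 68% in the unfavourable settings examined and near 95% in the others. The steps/day figures concern step count only. For WOMAC the mechanism is the same, but no separate calculation was made. The lack of a fixed target does not depend on the simulated numbers.

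**What to change.** Delete the significance rule. Before the data are analysed, pre-specify one primary model and one target for both primary outcomes: the 12-month effect over all randomised participants. Either of two specifications will do:

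- always include the COVID-19 restriction term, as a main effect only; or
- always keep the group-specific terms and average the contrast over observed restriction status at each visit.

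Report the other as a sensitivity analysis, with the same definition of restriction in both. The cost is wording in the analysis plan and at most one or two degrees of freedom spent on terms that may prove unimportant.

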### Randomisation allocation concealment and blinding

Following completion of the baseline assessments (questionnaires, objective assessment, accelerometry), participants are randomised to either the EPIPHA-KNEE group or the Best Practice Education/Activity Control group. The computer-generated randomisation schedule was prepared by the study biostatistician using Research Randomizer [50], with randomly selected permuted blocks of varying size (4 and 6) and using a 1:1 ratio to the two treatment groups within four strata (sex and site: Adelaide, Melbourne). The EPIPHA-KNEE intervention and the Best Practice Control intervention are provided by different physiotherapists located at different clinic sites. Thus, once allocated to an intervention group, participants choose one of the candidate physiotherapy clinics that provide that intervention to attend (i.e., the clinic that is most convenient for them).

Allocation is concealed using central automated allocation, with security in place to ensure data cannot be accessed or influenced. The randomisation schedule is stored within a password-protected electronic system (REDCap). A hard copy of the raw randomisation schedule is also stored in a secure location at each site should the electronic system fail. Only the unblinded Research Leads ([name] in Adelaide, KB in Melbourne) have access to raw copies of the randomisation schedules. The trial coordinators at each site (Adelaide, Melbourne), randomise participants to intervention group. Notably, while the trial coordinators determine if a participant is eligible for inclusion in the trial, due to inaccessible online randomisation with use of randomly permuted block size and stratification, they are unaware when this decision is made to which group the participant will be allocated. Once randomised, the (now) unblinded trial coordinators at each site (Adelaide, Melbourne) coordinate treatment appointment scheduling with the appropriate physiotherapist as identified by the participant.

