### Trial sample size

The Osteoarthritis Research Society International (OARSI) recommends an effect size (d = mean difference/SD_difference_) of 0.5 as the minimal clinically important difference (MCID) for outcomes in OA trials [97]. Past work has estimated that PSE increases physical activity by 1165 steps/day (SD = 985) in people with back pain, producing a large effect (d = 1.18) [39]. Given ~ 850 steps/day increase in knee OA populations after intervention (SD_difference_ = 950) [98] and our pilot data, we anticipate a moderate-large effect in the PSE group and a small effect in the control group at 12 months; consistent with a between group effect size of 0.5. Analysing these data using linear mixed effects modelling, to detect an effect size of d = 0.5 for physical activity using alpha = 0.05, power = 0.90, 4 time points, repeated measures correlation = 0.7, and 20% loss to follow-up [98], 156 participants (78/group) are needed. To additionally adjust for clustering based on therapist (~ 12 therapists/group; ~ 6.5 patients each; ICC = 0.05 [99]), 198 participants (99/group) are then required. The MCID for WOMAC Total at 12 months in people with knee OA undergoing an exercise intervention is 11.5 [100, 101], and given a between group SD from our pilot data of 13.8 (d = 0.83) [42], we are also sufficiently powered for this outcome. We did not adjust the alpha level for multiple comparisons (two primary outcome measures) in our power analysis, but we will present unadjusted *p*-values and confidence intervals for meaningful interpretation.

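### The treatment effect is specified as a contrast of change from baseline with no baseline adjustment named; on the natural reading this is unbiased but gives away precision that one sentence would recover

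*Protocol article*

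**What the plan says.** The Primary analysis section specifies a linear mixed model with a random intercept per participant, fitted separately to each outcome. On covariates it says "The model will include terms for stratification factors of sex and site", and it adds time-varying COVID-19 restriction terms. The treatment effect follows: "We will construct linear contrasts to compare the adjusted mean change in outcome from baseline to each time point", between the EPIPHA-KNEE and control groups. The baseline value of the outcome is not named as a covariate, and nothing says that the two arms share a baseline mean.

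Two other places bear on the point. The randomisation section says "Following completion of the baseline assessments (questionnaires, objective assessment, accelerometry), participants are randomised", so baseline values precede allocation. The Trial sample size section plans "to detect an effect size of d = 0.5 for physical activity using alpha = 0.05, power = 0.90, 4 time points", with "repeated measures correlation = 0.7, and 20% loss to follow-up". Outcomes are measured at baseline, 12 weeks, 6 months and 12 months, so four time points must include baseline, which suggests that it is treated as a response. The Analysis section calls this plan preliminary and promises a full statistical analysis plan.

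**The concern.** Because baseline is measured before randomisation, the arms have equal expected baseline means by design. A difference in change with baseline means free by arm ignores this. It subtracts the whole observed baseline difference (coefficient 1), whereas under a random-intercept model the efficient coefficient is the correlation, 0.7 at the planning value. The surplus 0.3 of the baseline difference is noise. If the arms differ at baseline by chance, 30% of that difference enters the estimate with reversed sign.

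At stake is the precision of the 12-month estimates. Validity is not affected.

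**Working it through.** **Inputs.** From Trial sample size: d = 0.5, alpha 0.05 (two-sided assumed), power 0.90, 4 time points, ρ = 0.7, 20% loss, ICC 0.05, about 6.5 patients per therapist, about 12 therapists per group, 99 per group. From Primary analysis: random intercept only, which implies compound symmetry.

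**The plan's own figure.**
- Two-sample formula: 2(1.960 + 1.282)²/0.5² = 84.06 per arm.
- Times the variance of the mean of four visits, (1 + 3 × 0.7)/4 = 0.775: 65.15.
- Times 1.2 for loss: 78.2, matching "156 participants (78/group) are needed".
- Times the design effect 1 + 5.5 × 0.05 = 1.275: 78 × 1.275 = 99.45, in line with "198 participants (99/group) are then required".

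The change-score factor 2(1 − ρ) = 0.60 gives 84.06 × 0.60 × 1.2 = 60.5 per arm, which does not match 78. Of the variants tried, only the mean of all four visits with loss applied as × 1.2 reproduces 156. The sample size therefore appears to be built on a different quantity from the contrast in Primary analysis.

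**Variance of the 12-month contrast**, in units of outcome variance divided by the number randomised per arm, at ρ = 0.7:
- Complete data, baseline means free: 2 × 2(1 − ρ) = 1.20.
- Complete data, baseline-adjusted: 2(1 − ρ²) = 1.02.
- Ratio (1 + ρ)/2 = 0.85, a loss of 15%.

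The gap is 2(1 − ρ)² = 0.18, the variance contributed by the surplus 0.3 of the baseline difference. Generalised least squares with 20% loss and all baselines observed gives the same gap on a larger variance:

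| Pattern of 20% loss | Free | Adjusted | Information lost |
|---|---|---|---|
| All directly after baseline | 1.455 | 1.275 | 12.4% |
| Spread over visits | 1.417 | 1.237 | 12.7% |
| Only at 12 months | 1.394 | 1.214 | 12.9% |

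A check with 150 simulated trials fitted by random-intercept models gave 12.7% against a constrained baseline and 12.4% against baseline as a covariate.

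**Therapist variance.** The plan's multiplicative design effect leaves these ratios unchanged. If therapist variance arises after baseline, adjustment cannot remove it, and 2 × 0.05 × m is added to both variances.
- m = 6.5 adds 0.65. Complete data: 1.67/1.85 = 0.903, loss 9.7%. With 20% loss spread over visits: 1.887/2.067 = 0.913, loss 8.7%.
- m = 99/12 = 8.25 adds 0.825. The losses are 8.9% and 8.0%.

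**Sensitivity to ρ**, without therapist variance:

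| ρ | Complete data | 20% loss, spread over visits |
|---|---|---|
| 0.5 | 25% | 21% |
| 0.7 | 15% | 13% |
| 0.8 | 10% | 8% |
| 0.9 | 5% | 4% |

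**Power for step count**, if d is in SD-of-change units and the design effect is multiplicative. The effective number is 99/1.275 = 77.65 per arm, and the effect is 0.5 × √0.60 = 0.387 outcome SDs. With loss spread over visits:
- Free: SE √(1.417/77.65) = 0.135, ratio 2.87, power 82%.
- Adjusted: SE √(1.237/77.65) = 0.126, ratio 3.07, power 87%.

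With all loss directly after baseline, the figures are 81% and 86%.

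**The case against.** The strongest reply is that the document never says baseline means are free by arm. In a model with a common baseline mean, the between-arm difference in change equals the between-arm difference at follow-up, and with baseline as a covariate, analysing change or follow-up gives the same treatment effect. The quoted sentence is therefore compatible with the remedy, and the article defers the full specification to a later plan. This stands as a limit: the free-baseline reading is an inference. It remains the natural one, because the section lists its adjustment terms and baseline is not among them. The two readings also give different estimates and intervals from the same data.

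It is also fair that the change contrast is unbiased with valid type I error, and that averaged over randomisations the imbalance term is zero. A reader who infers a biased or invalid primary analysis goes further than the documents allow.

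A reader might also infer that the trial has only about 80% power. That holds only for step count, with d in SD-of-change units and a multiplicative design effect. The plan does write "recommends an effect size (d = mean difference/SD_difference_) of 0.5", which supports those units, but its 156 reproduces on the outcome-SD scale. There the same unadjusted contrast has 0.5/0.135 = 3.70, about 96% power. For WOMAC, with the plan's d of 0.83 taken in SD-of-change units and 99 × 0.8/1.275 = 62 per arm, power exceeds 99%.

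**Conclusion.** The point holds as an efficiency issue. For any correlation below 1 under the stated random-intercept model, the free-baseline change contrast is less precise than a baseline-adjusted one.

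For step count at ρ = 0.7 the loss is 15% with complete data, about 12–13% with the planned 20% loss, and about 8–10% if therapist variance is added to both estimators. These figures rest on the free-baseline reading, compound symmetry and a planning correlation given for step count. It is tempting to carry one percentage over to both primary outcomes. The documents do not support that, since no correlation is given for WOMAC. This is a free improvement, not the correction of an invalid analysis.

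**What to change.** State one of two things in the statistical analysis plan:
- baseline is a response with means constrained equal across arms (visit effects, plus arm-by-visit terms at post-baseline visits only); or
- the baseline outcome is a covariate, with the 12-week, 6-month and 12-month values as responses.

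Report the 12-month adjusted mean difference as the treatment effect for both primary outcomes, and use the same form for secondary outcomes measured at baseline. Global rating of change has no baseline value and is unaffected. The sex, site and COVID-19 terms can stay. The cost is wording only: baseline values are already collected, and no participant or visit is added.
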